## Informed consent process for surveys

After recruitment, the interviewer will complete four tasks during the informed consent process:

1. Explain the study and answer any questions
2. Screen for eligibility
3. Obtain written informed consent
4. Inform the participant that s/he may be invited to participate in an additional IDI or FGD.

If the selected resident is eligible, the interviewer will capture the participant’s identifying name, identification number, address, telephone number, secondary telephone number, email address, and fingerprint scan using a tablet computer or personal digital assistant (PDA). The research team will use this information to contact the participant for the three follow-up interviews that are planned during the three-year duration of the study. Personal identifying information for study participants stored in an encrypted, password-protected file, and only made available to relevant study personnel. A full description data security measures is included in the “Data Management” section.

Before administering the baseline questionnaire, the interviewer will briefly explain the study and its objectives to the selected participant. If the participant is still interested, the interviewer will either read aloud or ask the participant to read the appropriate informed consent document (Annex A). At this point, the interviewer will confirm that the participant expects to be available to participate in three additional follow-up interviews over the next three years, noting that the participant may also be invited to take part in an IDI or FGD. Finally, the interviewer will respond to any questions and concerns the participant may express about the study, emphasizing that participation is voluntary and that refusal to participate will affect neither the community standing nor services they may receive from the CR program, and that s/he may discontinue participation at any time.

Once all questions are answered to the participant’s satisfaction, the interviewer will ask the participant to provide written consent as an indication that they understand the risks and benefits of the study, and voluntarily agree to participate. If the participant is illiterate, the interviewer will ask the participant to identify a person who can sign the consent form on the participant’s behalf. To complete the informed consent process, the interviewer will sign the consent form and provide a copy to the participant.

No person will be enrolled until written informed consent is obtained. Informed consent will be obtained without coercion, undue influence, or misrepresentation of the potential benefits and risks that might be associated with study participation. All information will be presented in a language that will be easily understood by participants. The consent form will describe the risks and benefits associated with study participation. Participants will be informed that they can refuse to answer any questions, stop the interview at any time, or withdraw participation in the study. One copy of the signed consent form will be given to the participant, another original copy will be kept in a locked file in MatCH Research Unit’s office, separate from other source documents that would link study data with participant identification.

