***Risks and benefits to participants***

*Risks:*

The primary risk associated with this study are possible breaches of participant confidentiality, as well as exposure to sensitive questions during the study interviews.

*Risks to confidentiality:*

Survey and interview content could include sensitive information that participants would not wish to be divulged to others. Data will be collected electronically, and every effort will be made to ensure that all study materials are stored securely. As this is a cohort study, data collectors will need to obtain contact information on all participants, but this information will be stored separately from collected data, and linking will be done through an identifying number. As detailed in the data management section, the research team will take all necessary precautions to ensure that participant contact information is never accidentally or intentionally made available to any non-privileged person.

*Additional risks:*

During the interviews, interviewers will ask sensitive questions about sex, HIV and other STIs, and GBV, which the participants could view as intrusive. As a result, some of the participants may become uncomfortable or distressed. The research team has designed the survey questionnaire to minimize unnecessary distress. The study team will pre-test the questionnaire among a small group of men and women to identify and eliminate unnecessary sources of discomfort or embarrassment. For the most sensitive questions around SGBV, the questions will be self-administered.

Similarly, the study team will train interviewers to be compassionate with participants, and to minimize their risk of distress. Experienced data collectors will conduct all study interviews, and interviewers will be instructed to stop questioning in cases where the participant shows signs of distress. The study will also establish a mechanism for referring distressed participants and victims of violence to a KwaZulu Natal public health facility for psychological counselling and survivor support services as needed.

*Benefits:*

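### The survey consent procedure ties capture of identity details and a fingerprint to eligibility rather than to signed consent

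*Protocol*

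**What the plan says.** The Protocol section Informed consent process for surveys describes the procedure twice.

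First comes a numbered list of four tasks. Task 1 is "Explain the study and answer any questions", task 2 is "Screen for eligibility", task 3 is "Obtain written informed consent", and task 4 is to mention a possible in-depth interview or focus group. Recording of identity and contact details has no place in the list.

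A narrative follows. Its first paragraph begins "If the selected resident is eligible, the interviewer will capture the participant" and names the items: "identifying name, identification number, address, telephone number, secondary telephone number, email address, and fingerprint scan". They are entered on a tablet or similar device, and the stated use is to reach the person for the three follow-up interviews. The next paragraph begins "Before administering the baseline questionnaire, the interviewer will briefly explain the study and its objectives to the selected participant". The consent form is then read, provided the person's interest has lasted, and the interviewer stresses that taking part is voluntary. The request for a signature comes after that.

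The same section ends with a safeguard: "No person will be enrolled until written informed consent is obtained". In Identification of study areas and eligible participants, the baseline survey is also placed after informed consent. The eligibility criteria there include willingness to give consent and willingness to supply an identity number, contact details and a fingerprint scan.

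**The concern.** The condition attached to taking identity details and a fingerprint is eligibility. Signed consent is not mentioned in it. A field team that builds its tablet form in the order of the narrative could record these items for someone who has not yet heard the consent form, and who may stop once it is read.

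The survey covers HIV, sexual behaviour and the experience or perpetration of violence. The Protocol itself says, under Risks and benefits to participants, "The primary risk associated with this study are possible breaches of participant confidentiality". An identity number and a fingerprint are the most identifying items the study holds. Taking them without written consent would add to the very risk the Protocol ranks first, and for people who may never contribute data.

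**Working it through.** No arithmetic applies. The check is to set the relevant places side by side and ask whether any of them makes capture wait for a signature.

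1. **Trigger.** The narrative makes capture depend on eligibility. In the task list, eligibility is settled at task 2 and written consent is obtained at task 3. An action triggered by eligibility therefore becomes permissible between tasks 2 and 3. This follows from the list itself and does not depend on the order of paragraphs.

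2. **Order of the narrative.** The sequence on the page is: eligible, record identifiers and fingerprint, explain the study, read the consent form if the person wishes to go on, confirm availability, stress that refusal carries no penalty, sign. Refusal is thus treated as open after the point at which capture is described.

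3. **List against narrative.** The list puts explanation before screening. The narrative describes explanation after a step that already presupposes eligibility, and times it only as before the questionnaire. The two disagree on when the study is explained, and neither says that capture follows the signature.

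4. **Safeguards.** The closing rule of the section covers enrolment. The rule under Identification of study areas and eligible participants covers the baseline survey. Neither mentions identifiers or biometrics, and whether recording them counts as enrolment is not stated.

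5. **Storage rules.** The consent section, Confidentiality and Data Management say how participants' identifying information is encrypted, separated and locked away. None of them covers a person who was screened, recorded and then declined.

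6. **The Protocol's own standard before consent.** For the household listing, Identification of study areas and eligible participants limits what is written down to age and initials. Taking an identity number and a fingerprint on eligibility alone would depart from that restraint. It would gain nothing, since the stated purpose of the identifiers is follow-up of people who have joined.

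The documents thus permit capture before written consent and describe it in that order, but do not say outright that it must come first.

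**The case against.** The strongest case against is that a loosely laid out paragraph is being read as a procedure.

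- **No time marker.** The capture sentence has no word such as first or then. The paragraph can be read as describing what is collected, why, and how it is stored. This is fair: precedence over the signature is inferred from the trigger and the layout. It does not remove the trigger, which names eligibility only.
- **Eligibility includes willingness.** Someone who says at screening that they will not consent or give a fingerprint is not eligible, and so does not reach capture. This narrows the group at risk. But willingness voiced at screening is not written consent, and the text still allows for people stopping afterwards.
- **Other wording points to capture after consent.** Follow-up contact uses details collected at baseline, and storage is described for participants. This suggests the intention was sound, but it sets no order.
- **Annexes are not shown.** The consent form, questionnaire and information sheets might fix the order and deal with people who decline. That possibility stands, and it is why the point is limited to the visible text.

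Two stronger readings are tempting. A reader might infer that a fingerprint is requested before the study has been explained at all. The documents do not support this: explanation is task 1 in the list, ahead of screening, and the household approach already includes an explanation and an information sheet for the adult or head of household. A reader might also infer that people who decline do have identifiers and a biometric on file. The Protocol nowhere says so; it is a possible consequence of following the text.

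**Conclusion.** The point holds as a defect in the consent procedure. Capture of identifiers and a fingerprint is conditional on eligibility rather than on signed consent, is described before the consent form is read and signed, and is not covered by the rules protecting enrolment and the survey. The task list and narrative also conflict on when the study is explained, and must be reconciled.

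The conclusion rests on two assumptions: that field staff follow the wording as it stands, and that no annex sets a different order. No count of affected people can be offered. The documents give no refusal rate after screening, and those unwilling to consent or give a fingerprint should already have been screened out. The change is worth making because it protects participants at almost no cost; it has no bearing on outcomes, sample size, power or analysis.

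**What to change.** In Informed consent process for surveys:

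- Change the condition so that identity details and the fingerprint are recorded only when the selected resident is eligible and has given written informed consent.
- Move that paragraph to follow the one in which the consent form is signed, and give capture its own place in the task list after written consent. List and narrative should then agree on when the study is explained.
- Set the screens of the tablet form in the same order, so that identifier and fingerprint fields open only after consent is logged.
- State that no identifying data are kept for people who decline.
- Check the annexed consent form, questionnaire and information sheets for consistency with the revised order.

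The cost is rewording and moving one paragraph, adding a line to the list and a sentence on people who decline, and a matching change to the tablet sequence. No extra visits, staff or participants are needed.

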***Risks and benefits to participants***

*Risks:*

The primary risk associated with this study are possible breaches of participant confidentiality, as well as exposure to sensitive questions during the study interviews.

*Risks to confidentiality:*

Survey and interview content could include sensitive information that participants would not wish to be divulged to others. Data will be collected electronically, and every effort will be made to ensure that all study materials are stored securely. As this is a cohort study, data collectors will need to obtain contact information on all participants, but this information will be stored separately from collected data, and linking will be done through an identifying number. As detailed in the data management section, the research team will take all necessary precautions to ensure that participant contact information is never accidentally or intentionally made available to any non-privileged person.

*Additional risks:*

During the interviews, interviewers will ask sensitive questions about sex, HIV and other STIs, and GBV, which the participants could view as intrusive. As a result, some of the participants may become uncomfortable or distressed. The research team has designed the survey questionnaire to minimize unnecessary distress. The study team will pre-test the questionnaire among a small group of men and women to identify and eliminate unnecessary sources of discomfort or embarrassment. For the most sensitive questions around SGBV, the questions will be self-administered.

Similarly, the study team will train interviewers to be compassionate with participants, and to minimize their risk of distress. Experienced data collectors will conduct all study interviews, and interviewers will be instructed to stop questioning in cases where the participant shows signs of distress. The study will also establish a mechanism for referring distressed participants and victims of violence to a KwaZulu Natal public health facility for psychological counselling and survivor support services as needed.

*Benefits:*

No immediate tangible benefit is likely to accrue to the participants through their participation; this will be made clear when obtaining informed consent. However the interviewers will describe the potential benefits of conducting this study, for health care systems and clients thereof, so that prospective participants are fully aware of how the data gathered will be used to provide programmatic recommendations and help others in their community.

***Confidentiality***

Prior to participant recruitment, the study protocol, recruitment materials, and instruments will be submitted to the Human Research Ethics Committee (HREC) at the University of Witwatersrand and the Population Council Institutional Review Board. Protection of human subjects will comply with USAID policy. In addition, permission will be sought from communities where the research is conducted.

The confidentiality of all participants enrolled in this research will be protected to the fullest extent possible. All staff involved in this study will receive appropriate training on research ethics, emphasizing the importance of informed consent and confidentiality. Interviewers will administer questionnaires in privacy. Completed questionnaires will be uploaded from the PDA each day to the central server housed at MatCH Research Unit’s offices. Electronic data will be encrypted and stored in password protected files.

All study records will be kept in a locked file cabinet accessible only to authorized members of the study team. All computer entry and networking programs will identify participants only by coded identification numbers. Interviewers will record the participant’s contact information directly into an encrypted and password protected file, where it will be linked to a unique study identification number. The list linking participant identification numbers to other identifying information will be stored separately from coded study forms and source records, in a locked file in a room with limited access in MatCH Research Unit’s office.

Data will be reported aggregately and participants will not be identified by name in any report or publication resulting from data collected in this study. Council staff will conduct monitoring visits to observe fieldwork and ensure interviewers’ adherence with confidentiality procedures. Match Research Unit will store study records until two years after publication of study findings, after which time records will be destroyed. If there is no publication, recordings will be erased no later than six years after the study has ended.

***Compensation***

Both female and male participants will be compensated for their time and for any travel costs related to participating in this research study. This is based on current participant compensation rates used by MatCH Research Unit in similar studies. Women and men who enroll in the cohort study and complete the survey will be paid R100 (~$14.00) for each round of data collection. If there is substantial loss to follow-up, we will consider increasing the compensation further for later rounds (to approximately R150 (~$21.00).

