#### e. Compensation

Both female and male participants will be compensated for their time related to participating in this research study. This is based on current participant compensation rates used by MatCH Research in similar studies. Women and men will be paid R100 (~$14.00) per interview for participating in a FGD or IDI.

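### The survey payment is worded as conditional on completing the survey, which works against the participant's right to stop and the interviewer's duty to stop for distress

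*Protocol*

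**What the plan says.** Four parts of the protocol bear on this.

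- **Compensation (survey).** The purpose comes first: "Both female and male participants will be compensated for their time and for any travel costs related to participating in this research study". The amount and its condition follow: "Women and men who enroll in the cohort study and complete the survey will be paid R100", per round of data collection. The same paragraph allows a rise to about R150 in later rounds if loss to follow-up is substantial.
- **Informed consent process for surveys.** "Participants will be informed that they can refuse to answer any questions, stop the interview at any time, or withdraw participation in the study". The same section sets the standard for consent: "Informed consent will be obtained without coercion, undue influence, or misrepresentation of the potential benefits and risks".
- **Risks and benefits to participants.** The protocol expects that "some of the participants may become uncomfortable or distressed" when asked about sex, HIV and violence. As one safeguard, "interviewers will be instructed to stop questioning in cases where the participant shows signs of distress".
- **Compensation for in-depth interviews (IDIs) and focus group discussions (FGDs) with cohort participants.** The amount is again R100, but it is paid "per interview for participating in a FGD or IDI".

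No section shown says what is paid when a survey interview ends early.

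**The concern.** Stopping is one of the study's protections against distress. A payment condition that only a finished interview satisfies works against it. It gives someone who would otherwise stop a reason to continue, or to hide distress from the interviewer. It also fits poorly with the stated purpose of the payment. A person who stops late in an interview of about 60 minutes, possibly after travelling to a community venue or the research offices, has spent most of the time and all of the fare. What is at stake is fair treatment of people who use a right that the protocol gives them, and consistency with its promise of consent free of undue influence. The situation can arise at baseline and at each of the three follow-up rounds.

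**Working it through.** The document gives no figure to reproduce here. The check is to apply the payment sentence, as worded, to each way in which an interview can end.

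| How the interview ends | Provided for in the protocol? | Time (and any travel) spent? | Meets the payment condition as worded? |
|---|---|---|---|
| All questions answered | Yes | Yes | Yes |
| Some questions declined, end reached | Yes (consent section) | Yes | Most naturally yes, though completion is not defined |
| Participant stops early | Yes (consent section) | Yes, in part or nearly all | No |
| Interviewer stops because of distress | Yes (risk section) | Yes, in part or nearly all | No |

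The last two rows hold the conflict. In both, the person has done only what the protocol permits, or has been stopped under the study's own safeguard, and still falls outside the condition.

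Three further comparisons:

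1. *Purpose against condition.* The opening sentence of the survey compensation paragraph covers time and travel without mentioning completion. The next sentence adds completion. The two agree only for interviews that run to the end.
2. *Assurances against condition.* The consent section says that refusing to take part has no effect on community standing or on services from the program. It does not mention payment, so it does not fill the gap.
3. *Survey against the other payments.* IDI and FGD members are paid for participating, and program staff are paid per interview. Of these payments, only the survey's carries a completion condition, and the survey is the instrument with the self-administered violence questions.

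For scale, each affected interview involves R100. Payment in full to the planned baseline cohort is 1,500 × R100 = R150,000. Each 1% of baseline interviews that ends early is 0.01 × 1,500 = 15 people, or 15 × R100 = R1,500. The document gives no early-stopping rate, so the actual number is unknown.

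**The case against.** The best reply is that this is loose drafting. The general sentence has no completion condition, the next one mainly fixes a rate per round, and completing the survey may mean no more than taking part in that round. The survey consent form (Annex A) and the information sheets (Annex K) are not shown and may already state what happens after an early stop. All of this is possible. It does not remove the point, because field staff would apply the sentence as written and it should agree with the annexes in any case.

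Three stronger readings are tempting, and the document does not support them:

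- *That distressed participants lose the R100.* This is only the literal consequence of the wording. Nothing in the text says that payment is refused or reduced for anyone.
- *That participants are pressed to continue.* This goes too far. Any question can be declined, so a person can skip every violence item and still reach the end. The most sensitive of these items are self-administered. When distress is visible, the interviewer ends the questioning. The incentive is confined mainly to someone who wants to end the whole interview, or who conceals distress.
- *That the rule biases the violence outcomes through selective dropout.* The document gives no rate of early stopping and no link from it to later loss. Payment is per round, and nothing says that an early stop forfeits later rounds. The primary comparison is between exposed and unexposed observations, so bias would require loss that differs by exposure, and nothing in the text points to that.

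**Conclusion.** The point holds as a conflict of wording with a modest effect on participant protection. The protocol states a completion condition that, taken literally, excludes interviews ended under its own stopping provisions. It thereby gives a financial reason to continue, of R100 per interview (about R150 if the later increase is used). This conclusion rests on the plain meaning of completion and on the absence, in the text shown, of any rule for partial interviews. If the consent form already pays for them, all that remains is to bring the compensation paragraph into line. Severity is minor, and nothing in the statistical analysis depends on it.

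**What to change.** Reword the payment sentence in the survey Compensation section so that every participant who begins the interview at a round receives that round's payment (R100, or the increased amount if adopted), whether questions are skipped, the participant stops, or the interviewer stops for distress. Make the same change in the survey consent form and information sheet if they carry the completion condition. This fits the stated purpose of compensating time and travel, and matches the basis on which IDI and FGD members are paid.

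The change takes one sentence in the protocol and, if needed, one in the consent documents. Its running cost is R100 for each interview that begins but does not finish, or R1,500 at baseline for every 1% of interviews affected. The downside is that a small number of payments will be made for partial interviews.
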